### Outcome measures

#### Observation chart data

The primary outcome will be the frequency of hyperactive delirium (‘terminal agitation‘), assessed using the modified Richmond Agitation and Sedation Scale (mRASS) [28]. The mRASS is a numerical scale that includes four levels of agitation: +1 = restless; +2 = agitated; +3 = very agitated; and +4 = combative. It should be noted that patients with pain/other problems may appear agitated, and so a diagnosis of hyperactive delirium (terminal agitation) must be validated by the clinical team’s use of an appropriate anti-psychotic or sedative drug to treat delirium (terminal agitation).

Other, secondary endpoints will be obtained through the observation chart, including oral intake, problems relating to parenteral fluids and any change in CAH status.

#### Process evaluation

A process evaluation will be undertaken in parallel to the feasibility study using a framework developed for cluster randomised trials [29] (based on the so-called RE-AIM framework [30]): data will be derived from routine research governance/trial monitoring (quantitative data) and additional/independent assessments (quantitative data, qualitative data). Thus, Principal Investigators from all units will be asked to complete a specifically developed questionnaire about the study processes at 1, 3 and 12 months after the start of the study (primarily quantitative data). In addition, clinical staff from 50 % of the units (randomly selected) will be asked to participate in focus groups about the study processes at 3–6 months after the start of the study (qualitative data).

### Data management

Investigator site staff will enter trial data into a paper CRF. The paper CRF is an Annotated Study Book (printed copy of the study eCRF) that has been reviewed by key trial staff including the Chief Investigator, Study Statistician and Trial Project Manager. Once the monitor has visited the site and completed the monitoring visit, completed pages will be stripped and returned to Surrey CTU for data entry into the eCRF. An eCRF will be set up in accordance with the protocol by a Data Manager and reviewed by another Data Manager, with range checks at point of entry and edit checks.

Point of entry checks fire during data entry, to reduce data entry errors. Range and edit checks will be examined by a Data Manager and queries generated as appropriate. Queries raised will be tracked by sending queries from and receiving answers to a Data Management mailbox. Surrey CRC will then update as appropriate.

### Statistical consideration

#### Sample size

Twelve sites (four hospitals, eight hospices) will be involved in the feasibility study, and these will be randomised to either standard intervention A or standard intervention B. There will be a separate randomisation process for the hospitals and the hospices. The target is to recruit 200 participants from the 12 sites within a period of one year; the end of the trial will occur when either 200 participants have been recruited, or the trial has been ongoing for one year (and inadequate numbers of participants have been recruited).

#### Analysis

A ’case‘ of hyperactive delirium is considered to be a participant that scores +2 to +4 on the mRASS [28], and is treated by the clinical team with an appropriate anti-psychotic or sedative drug to treat hyperactive delirium (terminal agitation). Participants who do not fall into this category will be considered as ’non-case‘. This dichotomous outcome will be used as the primary endpoint for the analysis.

The analysis evaluating the difference in proportions of participants experiencing hyperactive delirium between the two interventions will be a logistic regression with the occurrence of hyperactive delirium as the dependent variable and interventions (A or B), cluster and cluster type (hospital or hospice) as explanatory variables. The analysis will be based on the intention-to-treat (ITT) population, and will furnish estimates of the proportion of subjects suffering from hyperactive delirium for each intervention together with an estimate of the coefficient of variation of true proportions between clusters within each intervention arm. The latter of these estimates is an important requirement for determining the sample size aspect of a future cluster randomised study designed with adequate power to evaluate the impact of the intervention including CAH. It is judged that recruitment of 200 participants in 12 clusters in the feasibility study will provide a realistic estimate.

The logistic regression analysis will allow the testing of the hypothesis of no difference in the proportion of hyperactive delirium experienced between groups treated by either intervention. The intervention including CAH will be considered an improvement on the other intervention, in this and any future definitive study, only if the proportion of hyperactive delirium sufferers is reduced by at least 20 %.

It is considered unlikely that this statistical analysis of the feasibility study will be able to test this hypothesis with sufficient power, but its results, together with information gained from other aspects of the study management, will be used to design a definitive study.

From a statistical perspective, the estimates of the proportion of subjects suffering hyperactive delirium for each intervention, and the coefficient of variation of true proportions between clusters within each intervention, obtained from the feasibility study, will be used to determine the number of clusters and sample size necessary to detect a difference of 20 % in the proportion of hyperactive delirium sufferers between the interventions with 80 % power using a two-sided 5 % significance level. This calculation will form part of the design of the definitive study.

Should the number of clusters and sample size in the feasibility study retrospectively be found to provide the necessary power to test the hypothesis, the statistician will provide this information to the study team as input into their decision as to whether a definitive study is required.

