**Methods/design:**

The study is a cluster randomised trial to assess the feasibility of conducting an adequately powered, randomised controlled trial of clinically assisted hydration in patients with cancer in the last days of life. Twelve sites, four National Health Service (NHS) hospitals and eight NHS/voluntary sector hospices in the United Kingdom, will be randomised to give either standard intervention A: continuance of oral intake and regular mouth care, or standard intervention B: continuance of oral intake, regular mouth care and clinically assisted hydration. Patients will be included if they: i) have a diagnosis of cancer; ii) are aged ≥ 18 yr; iii) have an estimated prognosis of ≤ 1 week and iv) are unable to maintain sufficient oral intake (1 L per day, measured/estimated); and v) are able to give informed consent. Patients will be excluded if they have contra-indications to receiving clinically assisted hydration. The primary endpoint of interest is the frequency of hyperactive delirium (‘terminal agitation‘), and this will be assessed using the Modified Richmond Agitation and Sedation Scale (administered every four hours). Other data to be collected include the frequency of pain, respiratory secretions (‘death rattle‘), dyspnoea, nausea and vomiting, adverse effects to clinically assisted hydration and overall survival. In addition, data will be collected on the use of anti-psychotic drugs, sedative drugs, analgesics, anti-secretory drugs and other end-of-life medication. The study has obtained full ethical approval.

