### Study procedures

During the treatment period patients will be reviewed at least every four hours, and an assessment made as to whether or not certain symptoms are present, that is, hyperactive delirium (‘terminal agitation‘), pain, excess respiratory secretions (‘death rattle‘), nausea and vomiting, dyspnoea and urinary continence. Agitation will be given a score (see below), but the other symptoms will simply be recorded as present or absent. In addition, changes in regular medications, use of as required (PRN) medications, oral intake, urinary continence, and (if appropriate) parenteral fluids administered, adverse events relating to parenteral fluids and requirements for re-cannulation will also be noted. Data will be obtained from the participant’s observation chart and the participant’s drug chart(s); these documents are considered source documents in this study.

At the end of the study the researcher will record the participant’s outcome, including the date of death/withdrawal, and the reason for withdrawal (if appropriate). The end of study occurs when an individual participant either: a) survives for ≥ 14 days; b) dies (expected outcome); or c) is withdrawn from the study Table 2.

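### Participants withdrawn before any delirium event are scored as delirium-free, which lowers the case proportion of whichever arm loses more of them

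*Protocol article*

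**What the plan says.** Under Statistical consideration, Analysis, a case needs an mRASS score of +2 to +4 in a participant who also "and is treated by the clinical team with an appropriate anti-psychotic or sedative drug to treat hyperactive delirium (terminal agitation"). The next sentence reads "Participants who do not fall into this category will be considered as" non-case, and then: "This dichotomous outcome will be used as the primary endpoint for the analysis".

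The model is a logistic regression with "interventions (A or B), cluster and cluster type (hospital or hospice) as explanatory variables". On the population: "The analysis will be based on the intention-to-treat (ITT) population".

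Under Study procedures, a participant's study ends when he or she "survives for ≥ 14 days; b) dies (expected outcome); or c) is withdrawn from the study". Patients are reviewed at least every four hours until then, and the date of death or withdrawal and the reason for withdrawal are recorded.

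The Analysis section counts hydration as an improvement only if the proportion with hyperactive delirium falls by at least 20%, in this study and in any later definitive one. It then uses the estimated proportions, with the between-cluster coefficient of variation, to size the definitive study.

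**The concern.** For a participant who dies or reaches day 14 without a case, the ever/never outcome is known. For one who is withdrawn first, it is not: delirium may have followed. The rule does not separate the two, so unobserved time is recorded as time free of delirium. Because the population is intention-to-treat, these participants stay in the denominator.

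The error runs in one direction within an arm, since it can only lower the case proportion. Between arms it favours the arm with more early withdrawals, whichever that is. The affected proportions are those compared with the 20% criterion and carried into the definitive sample size. If withdrawal differs between sites, the between-cluster coefficient of variation is affected too.

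**Working it through.** **Figure to reproduce.** None. The article states no withdrawal rate, and the 200 participants are a judged target, not a calculated one.

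**Inputs.**
- Scoring rule, model and population: Analysis section.
- End of observation at death, withdrawal or 14 days: Study procedures.
- Delirium frequency of 25–85% at the end of life: Background. The values 25%, 50% and 85% are used for the true proportion p.
- Fraction w of an arm withdrawn before any event: assumed, 10% or 20%.
- Withdrawal unrelated to delirium risk: assumed.

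**Simple form.** Observed proportion = p × (1 − w), so the relative fall is w whatever the value of p.

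| True p | w = 10% | w = 20% |
|---|---|---|
| 25% | 22.5% (2.5 points lower) | 20.0% (5 points lower) |
| 50% | 45.0% (5 points lower) | 40.0% (10 points lower) |
| 85% | 76.5% (8.5 points lower) | 68.0% (17 points lower) |

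**Check with withdrawal spread over time.** Take constant daily hazards h (delirium), m (death) and v (withdrawal), with a 14-day cap. The proportion scored as a case is h/(h+m+v) × [1 − exp(−14(h+m+v))]. Mean survival of 3 or 4 days is assumed, h is set to give p without withdrawal, and v is set so that 10% or 20% withdraw before an event. The results are 22.5–22.6% and 20.0–20.1% for p = 25%, 45.0% and 40.0% for p = 50%, and 76.5% and 68.0% for p = 85%. The simple form holds closely.

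**Both arms.** The apparent relative reduction in arm B with no true effect is 1 − (1 − wB)/(1 − wA). With wA = 0 and wB = 10% it is 10%. With equal withdrawal it is zero, but both proportions are still too low: true values of 50% and 40% become 45% and 36% at w = 10%, so the absolute difference shrinks from 10 to 9 points.

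**Against the 20% criterion.** The article does not say whether 20% is relative or absolute. Read as relative, 10% loss in one arm alone produces half of it and 20% loss all of it. Read as absolute, 10% loss at p = 50% moves 5 of the 20 points.

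**What a two-way sensitivity analysis would show.** At p = 50% and w = 10%, scoring withdrawals as non-cases gives 45%, and scoring them as cases gives 45% + 10% = 55%. The gap equals w, so the reader sees how much rests on the scoring.

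**The case against.** **The sentence may only set a clinical boundary.** It could be meant for a score of +1, or for agitation from pain without delirium treatment, with incomplete observation left to an analysis plan that is not shown. That is a fair reading of its purpose. As worded, though, it covers everyone without a recorded case, and an analysis plan would have to depart from it to treat withdrawals otherwise.

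**Withdrawal may be rare or balanced.** This stands as a limit on size. Stopping fluids is not leaving the study: change in hydration status is a separate endpoint, and cannulation problems are recorded daily. Patients likely to be transferred are excluded at entry. A site's representatives may withdraw the cluster, but the article does not say that this ends observation of patients already enrolled.

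**Censoring has its own assumption.** It treats withdrawal as non-informative, which may be false. That is why the two-way scoring is needed beside it.

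**A stronger reading does not hold.** A reader might infer that the endpoint wrongly penalises an arm whose patients live longer, since survival is collected ("adverse effects to clinically assisted hydration and overall survival") and longer life means more assessments. With a constant delirium hazard of 0.15/day and mean survival of 4 against 5 days, the proportions are indeed 37.4% and 42.5%. With the hazard cut by 20% to 0.12/day in the longer-surviving arm, they are 37.4% and 37.1%. But both the constant hazard and the survival gain are assumed. The Background quotes a review that says lack of hydration hastens dying, but also reports no clear benefit to length of life. Death is the expected end of follow-up, and the proportion with treated agitation before death is a complete and legitimate quantity. Preferring another is a choice of estimand, not the correction of an error.

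Nor should the conclusion be made to agree with a rate per patient-day. Suppose 37.4% in both arms have onset in the last 24 hours of life, with the same survival means and the 14-day cap. The ever/never proportions are then 36.4% and 35.3%, close to equal. First cases per patient-day are 0.098 and 0.078, a rate ratio of about 0.80 with no true effect.

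**Conclusion.** The point holds for withdrawals. The article fixes a rule that records an unknown outcome as delirium-free, and this lowers the case proportion by the fraction withdrawn before an event, if withdrawal is unrelated to risk. The direction within an arm follows from the text. The size does not: w is assumed throughout, and if withdrawal is related to risk the fall will differ from w. Any statement that a given loss uses up a given share of the 20% criterion also depends on reading that criterion as relative or absolute.

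This is a feasibility study that does not expect adequate power, so the main consequence is for the planning proportions it passes on and for any use of the 20% criterion. The documents do not support extending the point to deaths.

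**What to change.** - Restrict non-case to participants observed without a case until death or day 14.
- Treat participants withdrawn before a case as censored at their last mRASS score.
- Beside the ever/never proportion, report the cumulative incidence of first case by arm, with death as a competing event (Aalen-Johansen), accounting for site.
- Add a sensitivity analysis that scores these withdrawals once as cases and once as non-cases, since withdrawal may be informative.

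The cost is a change of analysis wording and one or two extra outputs. Dates of death and withdrawal and the four-hourly scores are already recorded. The censored analysis brings the assumption of non-informative withdrawal, which the two-way scoring puts in view.

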## Methods

### Trial design and setting

The study will be a multi-centre cluster randomised trial carried out in NHS hospitals and NHS/voluntary sector hospices in the United Kingdom. Twelve sites (four hospitals, eight hospices) will participate in the feasibility study and will be randomised to either standard treatment A or standard treatment B. The Surrey Clinical Trials Unit, Surrey CRC, University of Surrey will be responsible for the cluster randomisation, trial management, data management and analysis.

The trial will assess the feasibility of a multi-centre RCT by identifying and addressing the methodological and ethical issues raised. It will provide primary and secondary endpoint data in order to design an appropriately powered RCT.

The trial has been funded by the Research for Patient Benefit Programme of the National Institute of Health Research (National Health Service) and has received a favourable ethical opinion from the London-Bromley National Research Ethics Service (NRES) Committee (reference 14/LO/1543), and the University of Surrey Research Ethics Committee. The trial, current protocol, version 5, 23 February 2015, is registered on ClinicalTrials.gov NCT02344927 (registered 4 June 2014).

Full informed written consent will be obtained from all patients, or their designated consultee, prior to enrolment in the trial.

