### Interventions

The interventions utilised within this trial represent current standards of care within clinical practice. Sites will be randomised to either ’standard intervention arm A‘ or ’standard intervention arm B‘, and this will become the standard of care within the site for the duration of this trial.

Standard intervention arm A involves:Continuance of oral intake (if appropriate)Regular ’mouth care’Standard management of pain and other symptoms in the terminal phase

Standard intervention arm B involves:Continuance of oral intake (if appropriate)Regular ’mouth care’Standard management of pain and other symptoms in the terminal phaseClinically assisted hydration, that is, parenteral fluids

Mouth care should be performed at least every four hours, and should correspond to the participating site’s policy/procedures for oral care in the terminal phase. Mouth care should be discontinued if it causes distress/discomfort to the patient.

The parenteral fluids may be administered either intravenously or subcutaneously at the discretion of the medical and nursing team [26]. The type of fluid to be administered is dextrose saline (4 % dextrose, 0.18 % sodium chloride), and the volume to be administered will be dependent on the patient's weight [27] Table 1.

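### The primary logistic regression lists site alongside two factors that are constant within site, so its intervention coefficient is not identified as written

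*Protocol article*

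**What the plan says.** The Analysis section of the protocol article defines a yes/no case of hyperactive delirium and compares the arms by a logistic regression with "interventions (A or B), cluster and cluster type (hospital or hospice) as explanatory variables". The same section says the analysis will give the proportion of cases per intervention and "an estimate of the coefficient of variation of true proportions between clusters within each intervention arm". It adds: "The logistic regression analysis will allow the testing of the hypothesis of no difference in the proportion of hyperactive delirium".

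The design is described elsewhere in the article:
- Sample size: "Twelve sites (four hospitals, eight hospices) will be involved in the feasibility study", and "The target is to recruit 200 participants from the 12 sites within a period of one year".
- Trial design and setting: the sites "will be randomised to either standard treatment A or standard treatment B".
- Interventions: the allocated treatment applies to the whole site, since "this will become the standard of care within the site for the duration of this trial".
- Sample size again: "There will be a separate randomisation process for the hospitals and the hospices".

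The article nowhere describes site as random or nested, and mentions neither generalised estimating equations nor a site-level analysis.

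**The concern.** Within a site every participant has the same intervention and the same cluster type. Once the model has a free parameter for each site, nothing is left for intervention or type to explain. The three terms stand in one undifferentiated list, so an analyst who follows the sentence literally would fit a model that cannot separate intervention from site.

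Three outputs depend on this sentence: the test between arms, the proportion per arm, and the between-site CV. The last two are the stated inputs to the sample size of the definitive trial. The article also allows the results to inform whether a definitive trial is needed at all. A coefficient that depends on software column order, or a standard error that omits between-site variation, could mislead that decision.

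**Working it through.** **Inputs.** From the article: 12 sites (4 hospitals, 8 hospices), 200 participants (200/12 = 16.7 per site), one intervention per site, type a property of the site. The article judges 200 participants in 12 clusters sufficient without a calculation, so there is no planned figure to reproduce. Assumptions: near-equal site sizes, a split of 2+2 hospitals and 4+4 hospices, and the case rates and CVs given below.

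**1. Rank of the stated model.** Write logit(p) = b0 + b1·intervention + b2·type + 11 site indicators.
- Columns: 1 + 1 + 1 + 11 = 14.
- Intercept plus 11 site indicators already have rank 12 and reproduce any function of site.
- The intervention column is a sum of arm-B site indicators, and the type column is a sum of hospital indicators. Neither adds rank.
- Rank is 12, so 14 − 12 = 2 columns are redundant. Neither b1 nor b2 is estimable. A numerical check over every 2+2/4+4 allocation gave rank 12 each time. This step needs no assumption about rates or CVs.

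**2. What software would print.** One simulated data set of 200 was refitted with different site terms omitted. The intervention coefficient ranged from −0.99 to +0.39 (standard errors about 0.7), while the log-likelihood stayed at −134.01. The data cannot choose between these values.

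**3. What remains estimable.** The mean of the arm-B site proportions minus the mean of the arm-A site proportions is estimable. Treating sites as fixed, its variance is taken as the sum over sites of p̂(1−p̂)/n, divided by 6² = 36. This omits between-site variance. Example with proportion 0.5, CV 0.25, n = 16.67:
- between-site variance = (0.25 × 0.5)² = 0.015625
- binomial variance = (0.25 − 0.015625)/16.67 = 0.01406
- true variance of a site proportion = 0.02969
- variance the model uses ≈ (0.25 − 0.02969)/16.67 = 0.01322
- ratio = 0.02969/0.01322 = 2.25, square root 1.50
- effective critical value = 1.96/1.50 = 1.31, a two-sided error of about 19%

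Simulation agrees (4,000 null trials per row, proportion 0.5):

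| Assumed CV | Averaged fixed site effects | Site-level model, 9 df |
|---|---|---|
| 0 | 5% | 4.9% |
| 0.15 | 11% | 5.2% |
| 0.25 | 20% | 5.2% |
| 0.35 | 29% | 5.1% |

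**4. Dropping site from the model.** With 12 × 17 participants and 20,000 null trials per scenario, the pooled comparison rejected in 6–32% for assumed rates of 25–50% and CVs of 0.15–0.40 (12% at rate 35%, CV 0.25). The site-level model rejected in 4.8–5.4% over the same scenarios.

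**5. Degrees of freedom.** Intercept, intervention and type use 3 of the 12 site values: 12 − 3 = 9.

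**6. The CV.** A model with fixed site effects has 12 free site parameters and no variance parameter. The raw variance of site proportions is not a substitute, because it includes binomial noise. At an assumed rate of 0.35 and n = 17:
- True CV 0.25: between-site variance (0.25 × 0.35)² = 0.00766; binomial variance (0.2275 − 0.00766)/17 = 0.01293; total 0.02059; apparent CV = √0.02059/0.35 = 0.41.
- True CV 0: total 0.2275/17 = 0.01338; apparent CV = √0.01338/0.35 = 0.33.
- After removing the binomial part: √(0.02059 − 0.01293)/0.35 = 0.25, and 0 in the second case.

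Even the corrected estimate is imprecise. At true CV 0.25 and proportion 0.5, the simulated 5th–95th percentile range per arm was 0 to 0.46, and 20% of estimates were zero.

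**The case against.** The strongest reply is that the article never calls site a fixed effect. It condenses a longer protocol, and an analysis plan may exist. Asking for a CV of site proportions suggests a hierarchical view, and with site as a random intercept the identification problem disappears. This stands as a statement of possible intent. It does not rescue the sentence: the article states a model instead of deferring it, gives all three terms the same role, and has no random-effect or site-level wording anywhere. A plan that used a random effect would have to depart from this text.

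A reader might infer that the plan can yield no treatment comparison at all. The document does not support that: the arm averages of the site effects are estimable, and their fault is the standard error. A reader might also infer that the CV is out of reach. It is not: a moment estimator on the 12 site proportions gives it, though the regression itself does not.

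Finally, this is a feasibility study whose authors expect too little power for the test. That lowers the weight of the type I error figures. The proportions and CV still feed the next trial's design, and the article still plans the test and applies its criterion for improvement to this study as well as to a later one.

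**Conclusion.** The concern holds for the model as stated. With site as an ordinary explanatory variable, the intervention coefficient is not identified (rank 12 for 14 columns), whatever the rates, CVs or allocation. The consequences for type I error depend on assumptions that the article does not supply. They are about 5–29% for averaged fixed site effects and about 6–32% if site is dropped, over the ranges shown in the working. The low ends are close to nominal, and the high ends need large between-site variation. The CV can be obtained, but only by a calculation that the article does not describe, and it will be imprecise with 12 sites. The point concerns the wording of the primary model and does not show that the trial cannot meet its aims.

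**What to change.** Replace the model sentence in the Analysis section with one of the following:
- a logistic model with intervention and cluster type as fixed effects, site as a random intercept and small-sample degrees of freedom, which is the smaller change to the present text; or
- a linear model of the 12 site proportions on intervention and cluster type, with t on 9 degrees of freedom.

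Add a sentence on the CV. Within each arm, take the observed variance of the site proportions, subtract the average binomial sampling variance, set a negative result to zero, take the square root and divide by the arm mean. Do not use the raw residual variance of the site-level model. Report the CV with its uncertainty, so that the definitive trial is sized over a plausible range and not on a single value.

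The cost is analysis wording only, with no new data. The downside is a wider confidence interval for the intervention effect, because it then includes between-site variation.

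### The design does not support the claim that 200 participants in 12 clusters will give a realistic per-arm between-cluster CV: the estimate will often be zero, and the trial sizes it implies span about three-fold or more

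*Protocol article*

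**What the plan says.** The Sample size section of the protocol article states: "Twelve sites (four hospitals, eight hospices) will be involved in the feasibility study". On recruitment it says: "The target is to recruit 200 participants from the 12 sites within a period of one year". The trial ends after one year even if fewer have been recruited. On allocation: "There will be a separate randomisation process for the hospitals and the hospices". The number of sites per arm is not given.

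The Analysis section specifies a logistic regression with intervention, cluster and cluster type as explanatory variables. Besides the arm proportions, it is to yield "an estimate of the coefficient of variation of true proportions between clusters within each intervention arm". The importance of this quantity is explicit: "The latter of these estimates is an important requirement for determining the sample size aspect of a future cluster randomised study". The adequacy claim follows: "It is judged that recruitment of 200 participants in 12 clusters in the feasibility study will provide a realistic estimate".

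The end of the section says that the proportions and "the coefficient of variation of true proportions between clusters within each intervention, obtained from the feasibility study" will determine the number of clusters and the sample size of the definitive study, for a 20% difference with 80% power at two-sided 5%. It adds that if the feasibility study itself proves, in retrospect, to have had the necessary power, this will inform the decision whether a definitive study is required. The section concedes low power for the hypothesis test but makes no similar reservation about the CV.

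**The concern.** A CV of true proportions is a between-site standard deviation divided by a mean, after the binomial noise within sites has been taken out. With about six small sites per arm, two things work against it. A standard deviation on so few degrees of freedom is poorly determined, and the noise to be subtracted can exceed the signal. The moment estimate can then fall to zero by chance, or come out at about twice the truth.

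This matters because supplying that number is a declared purpose of the study. The CV enters the cluster formula as a square, so its error is magnified in the trial size. A chance zero would under-size the definitive trial, and a chance high value would inflate it. The retrospective power check needs a CV as well, so a chance zero could also suggest that no definitive trial is needed.

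**Working it through.** The plan gives no precision figure for the CV, so there is nothing to reproduce; the check is whether the claim holds under plausible values.

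**Inputs from the protocol article.** 12 sites; 200 participants, so 200/12 = 16.7, taken as 17 per site; CV estimated within each arm; 80% power, two-sided 5%; a 20% difference, not stated to be relative or absolute.

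**Assumptions (not in the document).** Six sites per arm (two hospitals, four hospices), case rate 35%, true CV 0.25, and 17 per cluster in the definitive trial. The Background gives 25–85% for delirium of any kind, but no planning rate for the trial's case definition.

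**Signal and noise per site.**
- Between-site variance: (0.25 × 0.35)² = 0.0077
- Binomial variance: 0.35 × 0.65 / 17 = 0.0134

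The noise is about 1.7 times the signal.

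**Simulated CV estimate.** Beta-binomial sites of 17; CV² = [s² − p(1−p)/m] / p², set to zero when negative (s² = variance of the site proportions, m = 17).

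| Estimator | Zero estimate | 95% range |
|---|---|---|
| One arm, six sites | 31% | 0 to 0.57 |
| One arm, cluster type removed (4 df) | 35% | 0 to 0.61 |
| Pooled over arms, within type (8 df) | 25% | 0 to 0.51 |

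Over case rates of 25–50% and CVs of 0.15–0.40, the six-site estimate is zero in about 5–51% of studies.

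Even without binomial noise, the 95% chi-square limits on a standard deviation, √(df/χ²), are ×0.60 to ×2.87 on 4 df and ×0.68 to ×1.92 on 8 df.

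**Effect on the definitive trial.** Clusters per arm: c = 1 + (1.96 + 0.84)² [p0(1−p0)/m + p1(1−p1)/m + k²(p0² + p1²)] / (p0 − p1)², with k the CV. The squared term is 7.849 with unrounded normal quantiles.

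*Relative 20% (35% vs 28%).* 7.849/0.07² = 1601.8; binomial terms 0.01338 + 0.01186 = 0.02524; p0² + p1² = 0.2009.
- k = 0: 1 + 1601.8 × 0.02524 = 41.4
- k = 0.25: 1 + 1601.8 × (0.02524 + 0.01256) = 61.5
- k = 0.51: 1 + 1601.8 × (0.02524 + 0.05225) = 125
- k = 0.57: 1 + 1601.8 × (0.02524 + 0.06527) = 146

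The per-arm span is 146/41.4 = 3.5-fold; the pooled span is 125/41.4 = 3.0-fold.

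*Absolute 20% (35% vs 15%).* 7.849/0.20² = 196.2; binomial terms 0.01338 + 0.00750 = 0.02088; p0² + p1² = 0.145.
- k = 0: 1 + 196.2 × 0.02088 = 5.1
- k = 0.25: 1 + 196.2 × (0.02088 + 0.00906) = 6.9
- k = 0.57: 1 + 196.2 × (0.02088 + 0.04711) = 14.3

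The span is 14.3/5.1 = 2.8-fold.

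**Retrospective power check.** On the absolute reading, with one CV applied to both arms, six clusters per arm fall short at the true CV (6.9 needed) but look sufficient at an estimate of zero (5.1 needed).

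**Other rates.** In a separate simulation over case rates of 30–50% and true CVs of 0.20–0.30, the 95% range of trial sizes was 2.4- to 5.5-fold. At a CV of 0.10 about half the estimates are zero and the spread is nearer 2- to 2.6-fold. At a CV of 0.5 and rates of 40–50%, zeros are rare (2–5%) but the spread is wider. Unequal site sizes make zeros more frequent: at true CVs of 0.20–0.30 and a 50% rate, 21–36% against 12–27% with equal sizes.

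**The case against.** This is a feasibility study. It admits low power for its test, and nothing here affects allocation, data collection or participants. Intervals, pooling and handling of zeros commonly sit in an analysis plan, or in the definitive trial's protocol, so their absence from an article is no fault. That is right, and it limits the point: what is challenged is the positive statement that the estimate will be realistic, which the article does make.

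The sizes also rest on a CV, a case rate, a site split and a cluster size that the document does not give. The cluster counts depend strongly on whether 20% is relative or absolute: 41 to 146 on one reading, 5 to 14 on the other. This also stands, so both readings and a range of rates are shown. The ratio survives either reading.

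Three stronger readings are tempting but not supported:
- A reader might infer that the CV will be used as a bare point value. The text says that it will be used to determine the size; it does not exclude an interval or a sensitivity range.
- A reader might infer that hospital–hospice differences will be mixed into the CV. Cluster type is in the regression that is to yield the estimates, and whether the CV is taken within type is left open.
- A reader might infer that estimating by arm wastes half the data. That presumes a common CV in both arms, which the document gives no reason to assume; separate CVs allow for arms that differ.

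**Conclusion.** The point holds as an unsupported adequacy claim about a quantity that the plan itself calls important. Under the central assumptions, roughly one per-arm estimate in three is zero, the 95% range reaches 0.57 against a true 0.25, and the implied definitive trial varies about three-fold or more. The frequency of zeros depends on the assumed rate and CV; poor precision was found throughout the range examined. Recruiting fewer than 200, which the stopping rule allows, would make it worse. The practical risk is greatest in the retrospective power check on the absolute reading, where a chance zero alone could make six clusters per arm appear enough. The article does not show that the CV will be misused, only that the assurance given for it is not justified.

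**What to change.** 1. Replace the sentence claiming a realistic estimate with the expected precision of the CV under stated assumptions (sites per arm, case rate, true CV), for instance the per-arm figures above.
2. Report each arm's CV with a confidence interval. Also report a CV pooled over arms within cluster type (8 df; zero in about 25%, 95% range 0 to 0.51 under the same assumptions).
3. Show the definitive trial's size across the interval, and base it on a pre-stated upper confidence limit, for example the one-sided 80% limit, instead of the point estimate. Say whether 20% is relative or absolute.
4. State that a zero estimate is not evidence of no clustering, both in the sizing and in the retrospective power check.

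This changes wording and analysis only; sites, participants and data stay as they are. Pooling requires the assumption of a common CV in both arms and narrows the range only modestly, so it cannot replace the interval. Sizing on an upper limit will project a larger definitive trial.
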